### Allocation of intervention and waitlist control group

Randomisation will take place at team level. The randomisation is performed by a research assistant who has no knowledge about the teams, using randomizer.org. In this tool, teams are inserted as pairs: of each pair one team is assigned to the intervention group and the other to the control group. The waitlist control group will start the intervention after completing the 12-month follow-up questionnaire. The intervention and control groups are aware of their own allocation status, but not of the allocation status of other teams. The allocation status of teams are known to the researchers involved in this study. In case of close collaboration between multiple teams within a department, the department is randomised to avoid contamination between these teams.

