### Data management and analysis

Before the start of the project, all issues of data management will be addressed in a data management plan. For this, Radboud University has a tool, that includes feedback from Research Data Management (RDM) Support. Training and support in writing a data management plan are offered by the section RDM Support and the data steward of the institute. In order to check whether the research has been carried out properly and reliably, authorised persons within the Behavioural Science Institute or Radboud University and (inter)national supervisory authorities (for example, the Netherlands Authority for the Protection of Personal Data) are able to inspect the data. While research is ongoing, data will be stored on the Radboud University’s network. The server space allows for managed access to and the sharing of data between and among partners and guests during the project. Safe and secure storage of data is guaranteed by the Information Technology security and safety protocols of the campus network.

We will perform descriptive analyses (means, standard deviation, frequencies) on all outcomes and covariates. For the main analysis, we will perform linear mixed model analyses with need for recovery as primary outcome, and group (intervention/control) x time interaction as independent variable, taking into account potential confounding prognostic factors. Potential confounders are included in the model when they account for at least 10% change in the main effect size of the group x time interaction. We will take into account nesting of the data. Similar analyses will be done with the secondary outcome measures.

Main analyses are performed according to the “intention to treat” principle and the unit of analysis is on the individual level. In addition, we will perform a per-protocol analysis to take into account teams in the intervention group that did not participate in the intervention or did not implement the intervention as planned. Any cases of missing data will be dealt with by imputation.

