## Discussion

This study addresses a compelling need for change in working conditions within long-term care to retain and improve the sustainable employability of its staff. Since many organisations work with self-managing teams, a team level approach is recommendable. Therefore, the Healthy Working Approach focuses on team-specific challenges, which likely increases the acceptability of implemented solutions. To our knowledge the Healthy Working Approach is one of the first participatory interventions at team level, cocreated with long-term care workers. The intervention has a strong basis, since it builds on the successful participatory workplace approach [29–31] and draws from the Self-Determination Theory which recognizes the importance of fostering the needs for autonomy, relatedness and competence for people to thrive at work [16]. By conducting both an effect- and a process evaluation, we will provide insight in both the effectiveness as well as the barriers/facilitators of the implementation process of the Healthy Working Approach.

One of the challenges in this design will be to include teams that perceive staff shortage and related challenges, as participating in the intervention requires time and focus. Even though these teams can specifically benefit from the intervention, these issues can prevent teams from participating. During recruitment we will emphasise that even though participating is a time investment, it is a way to tackle current issues (and therefore likely to be beneficial long-term).

Although we use a randomised controlled design, where randomisation takes place at the level of the department or team, contamination cannot be completely avoided. Communication within the organization and between teams during the study can cause waitlist control teams to get knowledgeable of the intervention and its implications. Because waitlist groups are informed about the study, give their consent, are allocated to the waitlist control group, and fill in questionnaires they are arguable not completely untreated [52]. To avoid most contamination and disclosure of information of individual participants we plan to disseminate the results on group level after the intervention within participating organisations, in peer-reviewed journals, and at academic conferences. First results from the study are expected in 2022.

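### The added per-protocol analysis selects teams on implementation in the intervention arm only, so randomisation does not protect its contrast, and the bias could go either way

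*Protocol article*

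**What the plan says.** All of the analysis text is in the protocol article, Data management and analysis. The primary approach is clear: "Main analyses are performed according to the “intention to treat” principle". The effect of interest comes from a linear mixed model with "group (intervention/control) x time interaction as independent variable, taking into account potential confounding prognostic factors", so it is a difference between arms in change over time.

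The article then adds: "In addition, we will perform a per-protocol analysis", whose purpose is "to take into account teams in the intervention group that did not participate in the intervention or did not implement the intervention as planned". No matching rule is given for control teams. The wording does not say in so many words that the teams are excluded. Exclusion is the ordinary meaning of per-protocol, though, and no other method is named.

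Under Allocation of intervention and waitlist control group, teams are entered in pairs, one going to each arm, and "The waitlist control group will start the intervention after completing the 12-month follow-up questionnaire". The Process evaluation section already plans to record dose delivered, dose received and fidelity.

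**The concern.** Whether a team holds its meetings and carries out its plan is known only after randomisation, and within the 12 months it can be seen in one arm only. The control arm contains teams that would also have failed to implement, but nothing identifies them. The per-protocol contrast therefore sets a selected part of one arm against the whole of the other.

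This matters if the reasons for not implementing are related to the course of need for recovery. A plausible case is a team that loses staff after baseline. It has no time for meetings, and its members grow more fatigued. Dropping such teams from the intervention arm while keeping their counterparts among the controls would produce an apparent benefit without any effect of the intervention. Because staff may have been similar at baseline, neither the change scale nor baseline adjustment would remove it. What is at stake is how far the per-protocol result can be read as the effect when the approach is actually used.

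**Working it through.** The protocol gives no figure for this analysis, so there is none to reproduce. The check asks how large the bias could be, and in which direction, when the intervention has no effect. Lower need for recovery is better, so a negative shift favours the intervention.

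**Inputs from the Sample size calculation section:** SD 29.75, ICC for teams 0.025, minimum relevant difference 12 points. **Assumed, because the protocol gives neither:** the share *f* of intervention teams dropped (10 to 30%), and the gap *g* between dropped and kept teams.

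**1. General formula.** Dropping a share *f* of teams that score *g* points worse shifts the intervention mean by −*f* × *g*.

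**2. Size on the follow-up score, using the protocol's own variance.** The between-team SD is √0.025 × 29.75 = 4.70 points. With normally distributed team means and exactly the worst share *f* removed, the shift is −φ(q)/(1 − *f*) × 4.70, where q is the upper *f* quantile of the standard normal distribution.

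| Share dropped | Shift (points) | Share of 12 points |
|---|---|---|
| 10% | −0.9 | 8% |
| 20% | −1.6 | 14% |
| 30% | −2.3 | 19% |

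This is perfect selection on the outcome. Real non-implementation would track the outcome less closely and shift the follow-up mean less.

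**3. Direction on the planned effect.** For the group by time effect, the bias is −*f* × (gap at follow-up − gap at baseline). With *f* = 20% and illustrative gaps:

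- stable gap, 12 then 12: −0.2 × 0 = 0
- growing gap, 6 then 12: −0.2 × 6 = −1.2, favouring the intervention
- shrinking gap, 12 then 6: −0.2 × (−6) = +1.2, against the intervention

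The follow-up shifts in step 2 carry over in full to the group by time effect only if the dropped teams had no gap at baseline.

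**4. If the intervention works unequally.** Suppose, for illustration, that the dropped 20% would have improved by 18 points if they had implemented, and the rest by 10. The per-protocol figure is −10. The figure for all teams, had all implemented, is 0.8 × (−10) + 0.2 × (−18) = −11.6. Here the per-protocol result is the smaller of the two.

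**5. The alternative under no effect.** Control teams have no access before the 12-month questionnaire, so non-uptake is one-sided. The complier average causal effect is the intention-to-treat contrast divided by the share of intervention workers in uptake teams. If the intention-to-treat contrast is 0, so is this estimate, whatever the gap between teams. With 80% uptake, the divisor is 0.8, and both estimate and interval are about 1/0.8 = 1.25 times those of the intention-to-treat analysis.

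**The case against.** The strongest reply has four parts.

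- **Every per-protocol analysis has this weakness, and the article presents this one as additional.** That stands, and it limits the point to a secondary result. The exact per-protocol set may also be settled in an analysis plan that is not shown. But the article itself fixes that selection concerns the intervention arm only, and the waitlist design means that no later definition can apply the same rule to controls.

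- **The Discussion does not forecast which randomised teams will fail.** A reader might infer from "Even though these teams can specifically benefit from the intervention, these issues can prevent teams from participating" that the protocol expects under-staffed teams to be the ones dropped. It does not say so. The passage opens with "One of the challenges in this design will be to include teams that perceive staff shortage and related challenges" and answers with "During recruitment we will emphasise that even though participating is a time investment", so it concerns enrolment before allocation, which touches both arms. The inclusion rule that at least three members be willing to attend the meetings should also filter out some such teams. Staff shortage as a cause of non-implementation after randomisation is a reasonable inference, since the time burden falls after allocation, but it remains an inference.

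- **The direction is not fixed.** A reader might conclude that the analysis will favour the intervention. Steps 3 and 4 show otherwise, and the same Discussion sentence says that these teams may gain most. This stands in full.

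- **The size is modest.** A reader might assume a 12-point gap and 30% dropped, giving 0.30 × 12 = 3.6 points. Under the protocol's ICC and SD, the gap between the worst 30% of teams and the rest is only about 2.3/0.30 = 7.8 points, so 3.6 exceeds what perfect selection would give.

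**Conclusion.** The concern holds for the additional per-protocol analysis and nothing else. Its contrast is not protected by randomisation, because selection follows post-randomisation behaviour that can be observed in one arm only. A bias towards the intervention is plausible but not certain. On the follow-up mean, it is at most about 0.9 to 2.3 points for 10 to 30% of teams dropped, or about 19% of the 12-point difference at the top.

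That size rests on the protocol's ICC and SD, on normally distributed team means, on no true effect, and on the assumed share dropped. It grows with the square root of the ICC. On the group by time scale it depends on how the gap evolves. The documents do not support reading this as a threat to the primary conclusion, which comes from the intention-to-treat analysis.

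**What to change.** Replace the per-protocol analysis, or accompany it, with a team-level complier average causal effect:

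- use randomisation as the instrument;
- define uptake as at least one meeting held;
- give cluster-robust intervals;
- state the assumption that teams with no meeting are unaffected by their allocation. Teams know their own allocation, so this needs to be said openly.

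Label any per-protocol comparison that is kept as exploratory and not protected by randomisation. Do not rely on dropping whole pairs as a remedy. The article says that teams are entered in pairs but describes no matching, so removing the partner of a non-implementing team may take out an arbitrary control team and leave the selection in place.

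The cost is some wording and one extra model, since the process evaluation already plans to record dose and fidelity. The interval will be wider than that of a naive per-protocol analysis. The estimate also does not deal separately with teams that met but did not implement as planned; they count as uptake teams, and the process evaluation can describe them.

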### Process evaluation

We will perform a process evaluation to evaluate the barriers and facilitators of the implementation process of the Healthy Working Approach using a combination of quantitative and qualitative methods. For the process evaluation, we will gain insight into recruitment, reach, dose received, dose delivered and fidelity in order to monitor the adherence to the procedures [51]. In addition, we will investigate barriers and facilitators of the implementation and satisfaction with the Healthy Working Approach. Table 1 provides an overview of who is involved in what element of the evaluation to provide an insight in the effectiveness, barriers and facilitators of the implementation process.

**Table 1 Tab1:** Overview of process and evaluation set up of the Healthy Working Approach by means of source, type of info and data collection method

Source	Type of info	Data collection method
Facilitators	Evaluation of the training and coaching, and how they perceived their role during the working group meetings	Interviews
Working group members	Evaluation of the content and process of the three meetings	Evaluation forms and interviews
Intervention group participants	Evaluation of the Healthy Working Approach and how they experience the implementation of solutions	Additional questions during the 6 and 9 month follow-up questionnaire
Stakeholders in the long-term care organisation	Evaluation of the Healthy Working Approach	Interviews

## Discussion

This study addresses a compelling need for change in working conditions within long-term care to retain and improve the sustainable employability of its staff. Since many organisations work with self-managing teams, a team level approach is recommendable. Therefore, the Healthy Working Approach focuses on team-specific challenges, which likely increases the acceptability of implemented solutions. To our knowledge the Healthy Working Approach is one of the first participatory interventions at team level, cocreated with long-term care workers. The intervention has a strong basis, since it builds on the successful participatory workplace approach [29–31] and draws from the Self-Determination Theory which recognizes the importance of fostering the needs for autonomy, relatedness and competence for people to thrive at work [16]. By conducting both an effect- and a process evaluation, we will provide insight in both the effectiveness as well as the barriers/facilitators of the implementation process of the Healthy Working Approach.

One of the challenges in this design will be to include teams that perceive staff shortage and related challenges, as participating in the intervention requires time and focus. Even though these teams can specifically benefit from the intervention, these issues can prevent teams from participating. During recruitment we will emphasise that even though participating is a time investment, it is a way to tackle current issues (and therefore likely to be beneficial long-term).

Although we use a randomised controlled design, where randomisation takes place at the level of the department or team, contamination cannot be completely avoided. Communication within the organization and between teams during the study can cause waitlist control teams to get knowledgeable of the intervention and its implications. Because waitlist groups are informed about the study, give their consent, are allocated to the waitlist control group, and fill in questionnaires they are arguable not completely untreated [52]. To avoid most contamination and disclosure of information of individual participants we plan to disseminate the results on group level after the intervention within participating organisations, in peer-reviewed journals, and at academic conferences. First results from the study are expected in 2022.

## Data Availability

Data sharing is not applicable to this article as no datasets were generated or analysed during the current study. A de-identified dataset will be made available once the study is completed.

## Abbreviations

ICC: Intraclass Correlation
RDM: Research Data Management
SD: Standard Deviation
SMART: Specific, Measurable, Achievable, Relevant and Timebound
